**III.e. Statistical Analysis**

**Step 1**: socio-demographic, clinical and epidemiological description of the groups, using the usual procedures of descriptive statistics such as calculation of frequencies, measures of central tendency and dispersion;

**Step 2**: characteristics will be compared between groups at the baseline, using one-way analysis of variance (ANOVA) for continuous variables and chi-square test for categorical variables;

**Step 3**: Shapiro-Wilk test will be performed to assess normality assumption of the outcome variables;

**Step 4**: analysis of paired and independent samples using the t-test for comparison within each group and between intervention groups, or applying equivalent non-parametrics tests (according to Shapiro-Wilk test results), before and after intervention;

**Step 5**: Person's chi-square to evaluate blinding effectiveness, comparing between groups.

These analysis will be performed through Stata, version 12.0 for Windows. Results will be considered statistically significant if p ≤ 0.05.

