**III.b. Population**

Patients with attention deficit hyperactivity disorder will be recruited by letter and email to the Psychiatric Association of Bahia (APB), Bahia Neurology Society (SNB) and the Brazilian Association of Neurology, Psychiatry and Allied Professions (ABENEPI) - chapter Bahia. We will also contact by mail and telephone, professional experts in ADHD, inviting them to refer potential patients for the study. We will also publish advertisements on the internet and on social networks, from October 2012 to December 2012, according to the inclusion criteria.

III.b.1. Inclusion criteria

-Ability to understand and sign the informed consent form;

-Diagnosis of attention deficit-hyperactivity disorder according to DSM-IV-TR and Adult Self-Report Scale (ASRS);

-Residents in Bahia;

-18 years old or older;

III.b.2. Exclusion criteria

-Major psychiatric disorders such as schizophrenia and bipolar disorder;

-Inability to understand the questionnaires applied (cognitive impairment- score ≤ 24 on the Mini-Mental State Examination) or illiterate;

-Abuse of psychoactive substances or alcohol, except nicotine and caffeine, during the last 12 months.

III.b.3. Sample size

This will be a randomized sample of ADHD individuals recruited through Internet media, social networks, and contact with ADHD experts and specialized societies of neurology, psychiatry and related fields, during the study period. A sample size of 50 subjects was calculated assuming a difference in proportion between the active tDCS and sham control groups of 40% on the Go/ No go performance, before and after interventions.

This calculation was performed using the statistical program STATA 12.0, considering an alpha of 0.05 and a power of 0.80, resulting in an sample of 25 subjects in each group, intervention and control. To address unexpected factors, we applied a drop-out rate of 20%, reaching a total sample size of 60 individuals.

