**III.d. Procedures**

After screening through psychiatric interview, explanation about all steps of this study, and agreement expressed through signed informed consent form, ADHD patients will underwent a cognitive evaluation through the Mini-mental state examination (MMSE), Mini International Neuropsychiatric Interview Brazilian (MINI PLUS), Adult Self-Report Scale (ASRS), Quality Questionnaire life in Adults with ADHD (AAQoL), and an interview through a questionnaire. This evaluation script is an instrument based on the ADHD diagnostic criteria from DSM-IV-TR, and consists on epidemiological and clinical questions.

Individuals will be divided into two groups by block randomization, aiming at a balanced distribution between the groups (30 subjects each). Blocks shall be composed of 10 subjects, totaling six blocks. To compose each group will be called 5 individuals from each block.

Following it, the brain electrical activity will be recorded by EEG with 32 channels placed on the scalp acoording to the 10-20 EEG international system, during 5 minutes. The recording will be in a resting state, the first minute with eyes open looking for a fixed point, and the last 4 minutes with eyes closed. Then, participants will be asked to perform tasks on the computer: two Go / No go tasks adapted from the original version, the first using as a target a fruit and the second a letter. After the cognitive tasks, subjects will undergo active or sham stimulation, according to the previous randomization.

Participants of the intervention group will be submitted to tDCS at 1mA, anodal electrode over the left dorsolateral prefrontal cortex and cathodal electrode over the equivalent area on the right side. On control group subjects (sham group), electrodes will be placed at identical positions and sham stimulation will be applied. The stimulation device will turn on for only 30 seconds so that the patient will feel the initial sensation, then shutting down. The intervention and sham procedure will take place in one single session of 20 minutes to evaluate the immediate effect.

At the end of the intervention, subjects will perform again two Go/ No go tasks (randomly selected to avoid learning effect), and they will undergo another EEG recording, with the same previous technical caracteristics.

This study will be performed at Laboratory of Functional Electrostimulation at Federal University of Bahia.

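### Step 2's baseline significance tests between randomised arms are uninformative; separately, Step 4's unadjusted between-arm test gives up precision that pre-specified baseline adjustment would recover

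*Protocol*

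**What the plan says.** Protocol section III.d forms the arms by chance: "Individuals will be divided into two groups by block randomization", in six blocks of 10 with five per arm from each block, giving 30 per arm. No stratification factor is named.

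Section III.e then sets out the analysis in steps:

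- Step 1 describes the groups' socio-demographic, clinical and epidemiological characteristics.
- Step 2 adds hypothesis tests: "characteristics will be compared between groups at the baseline, using one-way analysis of variance (ANOVA) for continuous variables and chi-square test for categorical variables".
- Step 4 is the efficacy analysis: "analysis of paired and independent samples using the t-test for comparison within each group and between intervention groups", or non-parametric equivalents depending on the Shapiro-Wilk result. It names no covariate. It refers to measurements before and after the intervention, but does not say whether the between-arm test uses post-stimulation scores or changes.
- One general rule closes the section: "Results will be considered statistically significant if p ≤ 0.05".

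Under section III.d, the Go/No-go tasks are performed before and after stimulation. MMSE, MINI-Plus, ASRS, AAQoL and an epidemiological and clinical questionnaire are collected beforehand.

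**The concern.** Two separate choices are at issue.

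First, a significance test of a baseline characteristic between randomised arms asks whether the difference could have arisen by chance, and randomisation has already answered that. What matters is the size of the imbalance and how strongly the variable predicts Go/No-go performance. The p-value measures neither. Over many characteristics, some tests will be significant by chance alone.

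Second, Step 4 fixes an unadjusted comparison although the trial measures the outcome itself before stimulation. In a trial of 60 this leaves available precision unused. If a prognostic variable happens to be unbalanced, nothing in the comparison corrects for it.

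**Working it through.** **Inputs from the protocol.** 30 per arm (III.d); p ≤ 0.05 (III.e), taken as two-sided because the side is not stated; planning figures of a 40-point difference in proportions, alpha 0.05, power 0.80 and 25 per arm before dropout (III.b.3).

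**Assumed.** Baseline-outcome correlation r of 0.3 to 0.7, equal SDs before and after, and a 0.8 SD effect for the power illustration. The protocol gives no SD or correlation.

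**1. The plan's own figure.** The two proportions are not given. The usual two-proportion formula, n = [1.96·√(2p̄(1−p̄)) + 0.842·√(p₁(1−p₁)+p₂(1−p₂))]² / 0.40², gives 23.3, so 24 per arm, at 30% against 70%. With continuity correction, 10% against 50% gives 24.1, so 25. The stated 25 is reproducible, and nothing below changes it.

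**2. What Step 2 can detect.** With two groups, one-way ANOVA is the two-sample t-test. The standard error of a standardised difference is √(2/30) = 0.258, and the critical t on 58 df is 2.002.

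- Smallest observed difference reaching p ≤ 0.05: 2.002 × 0.258 = 0.52 SD.
- An observed 0.4 SD difference: t = 0.4/0.258 = 1.55, p = 0.13.
- Power for a true difference of 0.3, 0.4 or 0.5 SD: 0.21, 0.33, 0.48. Power of 0.80 needs 0.74 SD.
- Chance imbalance per characteristic (normal approximation): above 0.3 SD in about 25% of randomisations, above 0.4 SD in about 12%.
- At least one spurious significant result among 10 or 20 independent characteristics (assumed counts): 1 − 0.95¹⁰ = 0.40 and 1 − 0.95²⁰ = 0.64.

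**3. Error of an unadjusted post-score test, given a realised imbalance D.** The shift is rD and the conditional standard error is 0.258·√(1−r²). The test still rejects beyond ±0.517 (2.002 × 0.258).

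| D (SD) | r = 0.3 | r = 0.5 | r = 0.7 |
|---|---|---|---|
| 0.174 (median) | 4.0% | 3.1% | 1.6% |
| 0.3 | 4.8% | 5.2% | 4.8% |
| 0.4 | 5.8% | 7.9% | 9.9% |
| 0.5 | 7.2% | 11.7% | 18.3% |

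Averaged over randomisations the error is 5%. The last two rows lie below the 0.52 SD threshold, so Step 2 would not flag them.

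If Step 4 means change scores and the unbalanced variable is the baseline Go/No-go score itself, the shift is (r−1)D against a standard error of 0.258·√(2(1−r)). At D = 0.5 the conditional error is then 14.4%, 11.7% and 8.9% for r = 0.3, 0.5 and 0.7.

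**4. Precision.** Variance of the treatment estimate, relative to the unadjusted post-score test:

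| r | Post score | Change score, 2(1−r) | ANCOVA, 1−r² |
|---|---|---|---|
| 0.3 | 1 | 1.40 | 0.91 |
| 0.5 | 1 | 1.00 | 0.75 |
| 0.7 | 1 | 0.60 | 0.51 |

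Power at 25 per arm for the assumed 0.8 SD effect (normal approximation) is 0.81 on post scores. With ANCOVA it is 0.84, 0.90 and 0.98 at r = 0.3, 0.5 and 0.7.

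**The case against.** A reader might infer that Step 2 decides whether the arms are comparable, that a non-significant result lets an imbalance pass as balanced, and that this is why the efficacy comparison is unadjusted. The protocol supports none of this. It says only that characteristics will be compared, and it attaches no decision rule or consequence to the result. The mention of balance in section III.d concerns equal group sizes. The lack of adjustment comes from Step 4 and would remain if Step 2 were deleted.

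A reader might also infer that the unadjusted test is biased or has an inflated error rate. Over randomisations it does not. Conditional error is near or below 5% for imbalances up to 0.3 SD. The larger figures need both an unusual imbalance and a strong correlation. Nothing in the protocol supports r of 0.5 to 0.7 for age or ASRS score, and ASRS is part of the inclusion criteria, which may narrow its range. At r = 0.2 to 0.3 the variance gain is only 4% to 9%.

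Step 4 may intend change scores, which would already use the baseline Go/No-go score. That stands as a reading, but ANCOVA still has (1−r²)/(2(1−r)) = (1+r)/2 of the change-score variance: 0.65, 0.75 and 0.85 at r = 0.3, 0.5 and 0.7.

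Finally, covariate lists are commonly left to a SAP, which is not shown and may exist. So the absence of a list is not the point. The point is that this protocol itself states the baseline tests and an unadjusted comparison.

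**Conclusion.** The point holds in two separate and modest parts. The Step 2 tests are uninformative: they test a null known to be true and flag only observed differences of about 0.52 SD or more. Removing them alone changes no efficacy result.

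The useful part concerns Step 4. Its between-arm test is valid on average but less precise than it could be, and it is exposed to chance imbalance in a prognostic variable. The gain from adjustment rests on the unknown baseline-outcome correlation: a variance cut of about 9% to 49% for r from 0.3 to 0.7, relative to a post-score test. The pre-stimulation Go/No-go score is the natural covariate because it is the same measurement taken earlier. The case for age or ASRS score is weaker. Sample size and alpha are unaffected. This is a minor improvement, not an invalidating error.

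**What to change.** - In Step 2, delete the ANOVA and chi-square tests. Keep the Step 1 description by arm, with standardised differences if wanted.
- In Step 4, make the between-arm Go/No-go comparison an ANCOVA of the post-stimulation score with the pre-stimulation score as covariate. Add at most one or two named characteristics already collected, such as age or ASRS total.
- State that these covariates are included whatever imbalance is seen, and that none is added or dropped because of a baseline p-value.
- Say how non-normality is handled, since a rank test does not carry covariates directly. Rank-based ANCOVA, or robust or permutation inference for the adjusted model, would serve.

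The cost is a few sentences of protocol text and one to three of the 58 degrees of freedom. No new data or patients are needed. The covariates should be fixed before any outcome data are seen.

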**I. OBJECTIVES**

I.a. General

To assess the neurobiological aspects associated with attention deficit-hyperactivity disorder (ADHD) and the contribution of transcranial direct current stimulation (tDCS) on inhibitory control.

I.b. Specific

I.b.1. To assess the contribution of transcranial direct current stimulation, comparing it to sham intervention, on the modulation of inhibitory control in adults with ADHD through Go/ No go task;

I.b.2. To examine the neurobiological aspects evidenced through the brain electrical activity observed by power analysis of frequency bands in patients with ADHD, using quantitative electroencephalography;

I.b.3. Proceed the Reconstruction of Functional Brain Network, of each participant, based on the quantitative EEG data through mathematical-computational modeling;

I.b.4. To register indicators of quality of life in adults with attention deficit-hyperactivity disorder through the Quality of Life Questionnaire for Adults with ADHD (AAQoL);

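### Step 4 does not say which test compares tDCS with sham, gives within-arm tests the same standing as between-arm tests, and does not adjust the between-arm comparison for the pre-stimulation score

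*Protocol*

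**What the plan says.** Objective I.b.1 is a comparison with a control: to assess tDCS by "comparing it to sham intervention, on the modulation of inhibitory control in adults with ADHD through Go/ No go task".

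Section III.e, Step 4, plans "analysis of paired and independent samples using the t-test for comparison within each group and between intervention groups". Depending on the Shapiro-Wilk result, rank-type alternatives replace the t-tests, and the sentence closes with a timing phrase that ties the tests to the periods before and after stimulation. One rule covers everything: "Results will be considered statistically significant if p ≤ 0.05". No test in the list is named as the one that answers Objective I.b.1, and no baseline-adjusted model, group-by-time term or between-arm test of change is stated.

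Under III.d, every participant has a resting EEG, does two Go/No go tasks, receives one 20-minute active or sham session, does two more Go/No go tasks, and then has a second EEG. The same section says the repeat tasks are selected at random to guard against learning. A pre-stimulation value of the task score and of the EEG measures therefore exists for everyone.

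**The concern.** A paired test inside the active arm does not compare anything with sham. It estimates the tDCS effect plus whatever else changes between the two measurements: general practice, fatigue and, for the EEG, the fact that the first recording precedes all tasks and the second follows both rounds of them. The sham arm is there to remove these shared changes, and it does so only when the arms are compared directly. Finding the active arm significant and the sham arm not significant is not a test of the difference between them.

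Because Step 4 lists both kinds of test under one significance rule, a reader of the results could not tell which p-value was meant to carry the conclusion. Separately, the between-arm comparison, as most plainly read, sets aside a baseline measurement that has already been collected and could sharpen it.

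**Working it through.** **The plan's own figure.** The sample size is derived by "assuming a difference in proportion between the active tDCS and sham control groups of 40% on the Go/ No go performance", "considering an alpha of 0.05 and a power of 0.80", "resulting in an sample of 25 subjects in each group, intervention and control". The two arm proportions are not given. Assuming 0.10 v 0.50, two-sided: n = [1.96·√(2·0.30·0.70) + 0.842·√(0.09 + 0.25)]² / 0.40² = 1.761² / 0.16 = 19.4. With continuity correction this is (19.4/4)·[1 + √(1 + 4/(19.4·0.40))]² ≈ 24.1, so 25. Other proportions give 16 to 24 per arm without correction and 20 to 29 with it. So 25 is reproducible under assumed proportions, and I use 25 analysable per arm below. The calculation concerns proportions, so it does not give the power of the t-tests in Step 4.

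**What each test estimates.** Let δ be the tDCS effect and g the change shared by both arms.

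| Test | Estimates |
|---|---|
| Paired, active arm | δ + g |
| Paired, sham arm | g |
| Between arms, before | 0 by randomisation |
| Between arms, after | δ |
| Between arms, change | δ |
| ANCOVA of post on arm and pre | δ |

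**Within-arm tests when δ = 0.** Let dz be g divided by the SD of the individual changes (an assumption; the protocol gives no value). With n = 25 the test statistic is noncentral t with 24 df and noncentrality dz·√25, and the two-sided 0.05 critical value is 2.064. With p the chance of significance in one arm, active significant and sham not has probability p(1 − p).

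| dz | Noncentrality | p | p(1 − p) |
|---|---|---|---|
| 0.2 | 1.0 | 16% | 0.16 × 0.84 = 13% |
| 0.36 | 1.8 | 41% | 0.41 × 0.59 = 24% |
| 0.4 | 2.0 | 48% | 0.48 × 0.52 = 25% |
| 0.5 | 2.5 | 67% | 0.67 × 0.33 = 22% |
| 0.7 | 3.5 | 92% | 0.92 × 0.08 = 7% |

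The last column cannot exceed 25%. With no shared change it is 0.025 × 0.95 = 2.4% (active improving, sham not significant).

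A simulation (20,000 trials per setting, 25 per arm, pre-post correlation 0.5, where dz equals the gain in SD) agrees. Gains of 0.2, 0.3 and 0.5 SD give a significant active arm in 16%, 30% and 67% of trials. The between-arm post test rejects in 5.3%, 5.2% and 4.6%, and the between-arm change test in 4.9%, 4.7% and 5.0%. Both hold their level.

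**Precision of the between-arm test.** With SD 1 and pre-post correlation r, the effective SD is 1 (post only), √(2(1 − r)) (change) or √(1 − r²) (ANCOVA). For an assumed true difference of 0.5 SD and 25 per arm, noncentrality is (0.5 / effective SD)·√(25/2).

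| r | Post only | Change | ANCOVA |
|---|---|---|---|
| 0.3 | 1.768 → 41% | 0.5/1.183·3.536 = 1.494 → 31% | 0.5/0.954·3.536 = 1.853 → 44% |
| 0.5 | 41% | 1.768 → 41% | 0.5/0.866·3.536 = 2.041 → 52% |
| 0.7 | 41% | 0.5/0.775·3.536 = 2.282 → 61% | 0.5/0.714·3.536 = 2.475 → 68% |

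Since 1 − r² = (1 − r)(1 + r) is at most 1 and at most 2(1 − r), ANCOVA is never less precise than either alternative, apart from the small cost of estimating one slope. For a larger assumed effect of 0.8 SD (normal approximation), post-only power is 81%, against 84%, 90% and 98% for ANCOVA at the same three values of r.

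**The case against.** The strongest reply is that a sound sham-controlled test is already planned. Step 4 includes independent-sample tests between the arms after stimulation, and these are protected against shared practice and fatigue. That stands in full.

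A reader might infer that the trial intends to claim efficacy from a significant active arm beside a non-significant sham arm. The protocol does not say so, and Objective I.b.1 points the other way. What can be said is that Step 4 does not rule it out, because no test is designated.

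A reader might also infer that the baseline is ignored altogether. The paired tests use it within each arm, and the closing timing phrase of Step 4 can be read as a between-arm test of pre-post change. The sample-size paragraph, which attaches a similar phrase to the between-arm difference, gives that reading some support. Such a test would be valid, but it is not stated and would not be more precise than ANCOVA. At r = 0.3 it is worse than ignoring the baseline.

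The random selection of repeat tasks is a real safeguard against learning specific items. It does not remove general practice with the task, and it does not make a within-arm test a comparison with sham.

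Finally, covariate adjustment is often left to a statistical analysis plan. That would answer mere silence. Here the protocol names its tests and gives those that cannot answer the objective the same standing as those that can.

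**Conclusion.** The point holds as a lack of designation plus an avoidable loss of precision. It does not show that the planned between-arm analysis is invalid.

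The risk of mistaking practice or fatigue for tDCS lies only in the within-arm tests. Its size depends on a shared practice effect that the protocol does not give: at dz of 0.2 to 0.5 and 25 per arm, about 16% to 67% for a significant active arm and about 13% to 25% for the active-yes, sham-no pattern. The second figure falls again when practice is strong.

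The gain from adjustment depends on the unknown pre-post correlation. For an assumed 0.5 SD difference it is about 3 points of power at r = 0.3, 11 at r = 0.5 and 27 at r = 0.7. Random selection of the repeat tasks could pull r towards the lower end. Adjustment also removes the effect of chance baseline imbalance in the score, which matters with about 25 per arm.

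**What to change.** In Step 4, name the test of the tDCS effect. For each outcome measured before and after stimulation, use a between-arm ANCOVA of the post-stimulation score on arm and the participant's own pre-stimulation score, reporting the adjusted difference with its 95% CI.

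Keep a fallback in place of the present switch to non-parametric tests: if the residuals are clearly non-normal, use a rank-based ANCOVA, or a permutation or bootstrap version of the same model.

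Label the within-arm pre-post changes as descriptive and state that no efficacy conclusion rests on them. Dropping the baseline p-values in Step 2 is optional. Under randomisation they test only chance, and removing them changes no effect estimate.

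The cost is a change of wording. No participants, visits or measurements are added.

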**III.c. Study Variables**

III.c.1. Dependent variables

The following variables will be evaluated: neuropsychological outcome (Go/ No tasks); power analysis of frequency bands through QEEG; and brain reconstruction network model of each individual by QEEG.

III.c.2. Independent variables

Transcranial direct current stimulation and sham procedure.

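### A Shapiro-Wilk result chooses between t-tests and rank tests in Steps 3 and 4, and neither branch specifies a between-arm comparison adjusted for the baseline score

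*Protocol*

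**What the plan says.** Protocol section III.e, Step 3: "Shapiro-Wilk test will be performed to assess normality assumption of the outcome variables". Step 4 then prescribes "analysis of paired and independent samples using the t-test for comparison within each group and between intervention groups". The same step gives the alternative that the normality check can trigger: "or applying equivalent non-parametrics tests (according to Shapiro-Wilk test results), before and after intervention". Section III.e closes with "Results will be considered statistically significant if p ≤ 0.05".

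Section III.c sends three kinds of outcome through this rule: Go/No-go results, QEEG band power and the network model. Section III.d has each participant do two Go/No-go tasks before stimulation and two after it, and records the EEG at both times. A baseline therefore exists for every participant.

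Section III.e does not say whether the between-arm test is on post-stimulation scores or on change, and it names no baseline covariate in either branch.

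**The concern.** The efficacy test is picked after the outcome data are seen. The two branches are not equivalent in what they estimate: a t-test addresses a difference in means, a rank test a shift between distributions. A normality pre-test would thus settle the hypothesis and the reported effect measure. Go/No-go scores, band power and network measures could each end on a different method, as could the within-arm and between-arm tests of one outcome.

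Separately, the between-arm comparison is an independent-samples t-test or its rank counterpart. Neither adjusts for the baseline score. In a trial of 60 people with a single session, that is precision already paid for and not used.

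**Working it through.** **1. The plan's own size.** Section III.b assumes a 40-point difference in proportion with alpha 0.05 and power 0.80, and gives no base proportions. The usual two-sided formula is n = [1.96·√(2p̄q̄) + 0.842·√(p₁q₁ + p₂q₂)]² / 0.40².
- 30% vs 70%: (1.386 + 0.545)² / 0.16 = 23.3, so 24 per arm.
- 10% vs 50%: (1.270 + 0.491)² / 0.16 = 19.4, so 20 per arm, or 25 with continuity correction.

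The stated 25 per arm is reproducible. The checks below use 25 per arm (evaluable) or 30 per arm (randomised).

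**2. What the gate decides.** All inputs here are assumed. With Shapiro-Wilk at 0.05 in each arm and 25 per arm, at least one arm was rejected in 8–10% of truly normal data sets and in 98–99% of log-normal or skewed count data sets. With 30 per arm, 60 no-go trials and logit-normal error rates, rejection on post scores ran from 10% (mean logit 0, SD 0.6) through 25% and 56% (mean logit -0.5 and -1) to 93% and 99% (mean logit -1.5, SD 0.8; mean logit -2, SD 0.9). In another set of such runs, post scores were rejected in 93–96% of trials and change scores in only 30–36%. The two scales led to different branches in 62–67% of trials, and t-test and Mann-Whitney disagreed on p ≤ 0.05 in about 9–10%.

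**3. Type I error.** With 25 per arm and 2,500 runs per scenario, the gated rule on post scores gave 0.047–0.059 over normal, log-normal and count data. The Monte Carlo standard error is √(0.05·0.95/2500) = 0.004. In the scenario with 0.059, Mann-Whitney used without any gate gave 0.058, so the gate is not the cause.

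**4. Gate and adjustment separated.** Power, 25 per arm, standardised effect 0.8, assumed pre-post correlation r:

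| Scores, r | t post | rank post | gated post | t change | rank change | gated change | ANCOVA | rank ANCOVA |
|---|---|---|---|---|---|---|---|---|
| normal, 0.5 | 0.791 | 0.766 | 0.791 | 0.792 | 0.767 | 0.795 | 0.887 | 0.861 |
| normal, 0.7 | 0.798 | 0.777 | 0.799 | 0.947 | 0.934 | 0.948 | 0.973 | 0.958 |
| log-normal, 0.5 | 0.692 | 0.767 | 0.767 | 0.730 | 0.788 | 0.790 | 0.773 | 0.864 |
| log-normal, 0.7 | 0.706 | 0.777 | 0.779 | 0.896 | 0.944 | 0.942 | 0.902 | 0.958 |
| count, 0.5 | 0.704 | 0.766 | 0.767 | 0.734 | 0.780 | 0.779 | 0.790 | 0.850 |

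- Gate: the gated test is as powerful as the t-test on normal data and more powerful on skewed data (0.767 vs 0.692).
- Adjustment, like with like on post scores: 0.692 to 0.773 for the t-test family and 0.767 to 0.864 for the rank family (log-normal, r = 0.5).
- Limit: on log-normal scores, plain ANCOVA was 2 to 4 points below gated change scores (0.773 vs 0.790; 0.902 vs 0.942). Rank ANCOVA was 2 to 7 points above them.

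**5. Closed form.** Power = Φ(0.8 / (s·√(2/25)) - 1.96), where 0.8/√(2/25) = 2.828. The multiplier s is 1 for post scores, √(2(1-r)) for change and √(1-r²) for ANCOVA.
- Post scores: Φ(0.868) = 0.81 at any r.
- Change: 0.67, 0.81, 0.955 at r = 0.3, 0.5, 0.7.
- ANCOVA: Φ(2.828/0.954 - 1.96) = 0.84, Φ(2.828/0.866 - 1.96) = 0.90, Φ(2.828/0.714 - 1.96) = 0.98.

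**6. Error-count scores.** With 30 per arm, 60 no-go trials and a log-odds effect of -0.35 (odds ratio e^-0.35 = 0.70), ANCOVA power was 0.35–0.68, gated change 0.27–0.55 and gated post 0.26–0.52. The gain was about 8 to 13 points over change and 9 to 19 over post. The gate moved power by at most about 1.5 points against always using the t-test. Two further settings:
- mean logit -1.5, SD 0.8: post gated 0.279, t-test 0.268; change gated 0.450, t-test 0.455; ANCOVA 0.535.
- mean logit -2, SD 0.9: post gated 0.221, t-test 0.216; change gated 0.306, t-test 0.310; ANCOVA 0.380.

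Including these two, the gain runs from about 7 points (0.380 - 0.306) to 13 over change, and from 9 to 26 (0.535 - 0.279) over post.

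**The case against.** The rule is written down beforehand, is conventional, and does not inflate type I error. A statistical analysis plan, not seen here, may fix the Shapiro-Wilk threshold, the rank tests, the scale and any covariates. The sample size in section III.b also speaks of a difference "assuming a difference in proportion between the active tDCS and sham control groups of 40% on the Go/ No go performance, before and after interventions", and Step 4 uses similar words, so a test on change scores is a fair reading. Change scores use the baseline in either branch.

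Much of this stands. The missing threshold, test names and confidence intervals are not held against the protocol. If change scores are meant, the gain from ANCOVA is smaller and, with strongly skewed scores, may disappear for plain ANCOVA. What remains is that choosing by pre-test is stated text: an analysis plan faithful to the protocol inherits it.

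Three stronger readings might be inferred and are not supported.
- That the rank branch discards the baseline while the t-test keeps it. The independent t-test in Step 4 is equally unadjusted, the paired tests use the baseline in both branches, and a rank test on change would keep it.
- That the gate costs power. Against an ungated t-test on the same scores it costs almost nothing, and on log-normal data it helps.
- That Go/No-go scores will nearly always go to rank tests. The protocol gives no score definition, trial count or error rate, and the simulated rejection share runs from 10% to 99%.

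**Conclusion.** The point holds in a limited form. Steps 3 and 4 leave the tested hypothesis and the effect measure to a normality test on the trial's own outcomes, and these may differ between outcomes. This is a weakness of prespecification, with no demonstrated harm to the error rate and almost no power loss from the gate.

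The avoidable loss of precision has another source: neither branch specifies a baseline-adjusted comparison between arms. Its size rests on assumed score distributions, correlations and effects. With error-count scores it was about 7 to 13 points of power against change scores and 9 to 26 against post scores. With log-normal scores, plain ANCOVA gave no gain over gated change scores, though rank ANCOVA did. The change is worth making because it is nearly free, not because the present plan would give invalid tests.

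**What to change.** Delete Step 3 as a decision rule. In Step 4, name one between-arm test for the Go/No-go scores: ANCOVA of the post-stimulation score on arm and baseline score, reporting the adjusted difference with a 95% CI. State the score and its scale (raw or transformed) in advance, because section 4 of the working shows that plain ANCOVA gains little on strongly skewed raw scores. Keep a rank-based ANCOVA, or a permutation p-value re-randomising arms within the blocks of ten in section III.d, as sensitivity analysis. Use residual plots for description only. Since the gate also governs the QEEG and network outcomes, name one method for each of those as well.

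Removing the gate alone and keeping unadjusted t-tests would recover nothing and could lose power on skewed scores, so both changes belong together. The cost is analysis wording and slight extra programming. No further data are needed, because the baseline is already collected.
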